## Abstract

**Background:**

Older adults with cirrhosis are particularly vulnerable to developing frailty with poor outcomes including increased falls, physical disability, hospitalizations, and all-cause mortality. Current management of frailty among older adults with cirrhosis is limited to general lifestyle recommendations including increased exercise and optimized diet, and few studies examining exercise interventions include patients with Child Pugh Class B or C. Whey protein and creatine are well-studied supplements commonly used to improve physical performance in athletes and have recently demonstrated positive effect in muscle mass among older adults but have not been studied in patients with cirrhosis. Therefore, we aimed to evaluate the effect of creatine/whey protein supplementation on frailty in older adults with cirrhosis (Child Pugh Class A, B, C) engaged in Strength Training Intervention (STRIVE), a semi-supervised program practicing exercise, nutrition, and life skills.

**Methods:**

This study is a randomized, placebo-controlled trial including older adults (≥ 60 years) with cirrhosis evaluated at a single health center. We will recruit 200 patients informed by sample size calculations. Patients will be randomized 1:1, stratified by Child Pugh Class and gender. Participants who meet eligibility criteria will be automatically enrolled in a 2-week “ramp-up” period to assess engagement in the exercise portion of STRIVE prior to full enrollment into the 12-week study (STRIVE with creatine/whey protein supplementation vs placebo). We will assess health-related quality of life using Patient Reported Outcomes Measurement Information System (PROMIS-29 v 2.0), self-reported physical activity using Duke Activity Status Index (DASI), patient activation using Patient Activation Measure (PAM^®^), and diet quality by healthy eating index using DietID^®^ and Automated Self-Administered Dietary Assessment Tool (ASA24). Body composition scan (BIA), liver frailty index (LFI), and morphologic measurements including waist circumference, hip circumference, midarm muscle circumference, and triceps skin fold will be measured. The primary outcome will be physical frailty (by LFI); secondary outcomes will include health-related quality of life (HrQoL), physical activity, healthy eating index, and body composition.

**Discussion:**

Our results will help inform frailty-mitigating strategies among older adults with cirrhosis that can be used for patients prior to or on the liver transplant waitlist. The addition of supplementation with creatine/whey protein may add to the armamentarium of strategies to improve frailty within this vulnerable population.

**Trial Registration::**

NCT07029243 (Registration Date: 2025-05-15)

## Background

Frailty, the loss of physiological reserve and increased vulnerability to health stressors, is a common muscle dysfunction-related condition among older adults.^1, 2^ Among community-dwelling non-nursing home adults ≥ 65 years, an estimated 15% of patients are frail and 45% are pre-frail.^2^ Frailty is associated with poor health outcomes including increased hospitalizations, falls, and mortality.^1-5^ Among adults with cirrhosis, frailty occurs in 1 in 4 adults, independent of age, and leads to the development of malnutrition, portal hypertension, impaired ammonia metabolism, and sarcopenia, all of which lead to hepatic decompensation and worse frailty. ^6-13^ Older adults with cirrhosis, particularly with decompensation, are therefore a particularly vulnerable population of patients who develop compounded frailty from age-related and cirrhosis-related factors.

Several strategies have been evaluated to improve sarcopenia and frailty. Exercise and nutrition are mainstay therapies to mitigate frailty and sarcopenia among both older adults and patients with cirrhosis.^14-16^ Nutrition-specific therapies that lead to improved outcomes include nutritional counseling, nocturnal feeding, supplementation with branched-chain amino acids, and increased protein intake.^17, 18^ Exercise-specific interventions associated with improved outcomes include aerobic exercise, moderate exercise, tai-chi, yoga, and strength-training exercises.^18, 19^ Geriatric assessments and medication optimization have also been effective strategies to reduce hospitalizations and further functional decline.^2^ Finally, protein and creatine supplementation have been evaluated among older adults who are frail given their promising effects on exercise tolerance and rehabilitation among athletes.^20-24^ National guidelines recommend prescribing prehabilitation strategies, including protein supplementation and physical therapy, for adults with decompensated cirrhosis who are frail given the particularly high risk of mortality in this patient population.^8^

Creatine is a nitrogenous organic acid found predominantly in skeletal muscle (> 95%) in the form of phosphocreatine and free creatine. About half of the body’s daily requirement of creatine is derived from diet. Its role centers on the conversion between creatine and phosphocreatine which yields free energy in the form of adenosine triphosphate (ATP).^25^ Whey protein is a high concentration of essential amino acids that increase muscle protein synthesis rate particularly after resistance training.^26^ The combination of creatine with resistance training among older adults was associated with greater lean muscle mass strength compared to those with resistance training only.^27^ Similarly, the combination of whey protein and creatine supplementation in addition to resistance lead to improved muscle mass and strength compared to creatine supplementation alone or to placebo.^23^ Protein supplementation, including branched-chain amino acids, is a cornerstone of the management of frailty among patients with cirrhosis.^28^ However, the use of creatine/whey protein supplementation has not been evaluated among older adults with cirrhosis.

In this randomized trial, we aim to evaluate the efficacy of creatine/whey protein supplementation vs placebo, each combined with a semi-guided digital health application, Strength Training Intervention (STRIVE), focused on exercise three days a week, 30 minutes per session, personalized nutrition counseling, and life skills support on frailty among older adults with cirrhosis, including patients with decompensated cirrhosis. We hypothesize that patients undergoing STRIVE with whey protein/creatine supplementation will experience improved frailty compared to those undergoing STRIVE with placebo supplementation.

## Methods/Design

### Study design and setting

We will conduct a prospective double-blind placebo-controlled, two-arm randomized controlled trial at a single center (Fig. 1). To ensure patients in the study are able to navigate the STRIVE platform and perform exercises on STRIVE, all eligible patients will first be pre-enrolled in a two-week “ramp-up” period during which they will participate in a simplified version of the digital health program that includes weekly exercise videos, post-video surveys, and weekly telehealth check-ins with a physician and/or exercise specialist to monitor their weekly exercise and adjust exercise prescriptions as needed. Patients who achieve ≥ 80% engagement with app activities and scheduled check-ins during the ramp-up period will proceed to randomization. Patients enrolled in the study will be randomized to creatine/whey protein supplementation vs placebo supplementation and STRIVE digital health programming. The STRIVE digital health programming uses the same interface as the ramp-up but includes three pillars: exercise, nutrition, and life skills (Fig. 2). Activities in the app include pre-recorded exercise videos to be completed three times per week, educational videos and reading, and interactive quizzes and surveys. Patients also receive weekly physician or exercise specialist check-ins to monitor exercise progression and to recommend personalized modifications; weekly check-ins with clinical research coordinator for safety monitoring, app-related questions, and supplement adherence evaluation; and biweekly check-ins with a nutritionist to assess dietary habits and provide personalized dietary recommendations. Patients are evaluated in-person at baseline prior to the ramp-up period, at 6 weeks after enrollment into STRIVE, and at 12 weeks at completion of STRIVE.

LFI: liver frailty index, PAR-Q: Physical Activity Readiness Questionnaire for Everyone, PROMIS-29 v2.0: Patient Reported Outcomes Measurement Information System, DASI: Duke Activity Status Index, BIA: Bioimpedance analysis

### Inclusion Criteria

Inclusion criteria include adults ≥ 60 years old with confirmed diagnosis of cirrhosis (Child Pugh Class A, B, or C) and a liver frailty index (LFI) ≥ 3.8. Participants must also be up to date on variceal screening through either up-to-date endoscopy screening and/or surveillance or on beta blocker. All participants require access to a digital device and internet, ability to remain in the study for at least 3 months, and engagement in ≥ 80% of activities in the ramp-up period before enrollment into STRIVE.

### Exclusion Criteria

Patients who meet the following criteria will be excluded: (1) inability to safely take creatine/whey protein supplementation due to allergy to milk protein, (2) hemodialysis due to concern for possible renal effects of creatine/whey protein supplementation, (3) lack of internet-connected smart device, (4) no English language proficiency due to English interface of STRIVE, (5) on supplemental oxygen due to safe home exercise engagement and possible edema associated with creatine/whey protein supplementation, (6) or with a condition that would compromise the safety of the patient participating in home exercise including unstable angina, myocardial infarction within the past 6 months, uncontrolled arrhythmia, severe COPD, pulmonary embolism within 1 year, bone fracture within 1 year, severe osteoarthritis precluding exercise, or ≥ 2 Grade 2 hepatic encephalopathy. Additionally, patients who fail to meet exercise screening criteria based on the Physical Activity Readiness Questionnaire for Everyone (PAR-Q+)^29^ will be excluded from the study.

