### Randomization

Patients who meet eligibility criteria and complete the two-week ramp-up period will be randomized using a 1:1 allocation ratio to placebo vs creatine/whey protein supplementation and permuted blocks of sizes of lengths 2 and 4 by the statistician. Randomization will be stratified by Child Pugh score (A, B, C) and gender (women, men). Six randomization lists will be generated by the study biostatistician using R “randotools” package for each combination of stratification factors: A/female, B/female, C/female, A/male, B/male, C/male. The randomization list will be used to assign eligible and consented participants to one of the two trial arms of the study to the pharmacy. Patients will receive a blinded box of creatine/whey protein vs placebo in single daily sachets with instructions on use.

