### Measurements

#### Assessments

Baseline assessment will be completed prior to pre-enrollment into the ramp-up period (Fig. 3). Additional follow-up assessments will be completed at 6 weeks after enrollment into the study and 12 weeks at completion of the study. Assessment at baseline will include demographic characteristics, vital signs and physical exam, and the following questionnaires: Patient Reported Outcomes Measurement Information System (PROMIS-29 v 2.0) to measure health-related quality of life^30^ (HrQoL), Godin-Shephard Leisure Time Physical Activity Index (LTPA)^31^ and Duke Activity Status Index (DASI)^32^ to measure self-reported physical activity, the Patient Activation Measure (PAM^®^)^33^ to measure patient activation, and DietID^™^
^34^ and the Automated Self-Administered Dietary Assessment Tool (ASA24)^35^ to measure dietary patterns. PROMIS-29 v2.0 is an NIH-supported HrQoL measure of 29 questions that cover broad domains including physical function, anxiety, depression, fatigue, sleep disturbance, participation in social roles and activities, and pain intensity with built-in normative references to the US general population.^30^ The LTPA is a 3-question survey that measures how much strenuous, moderate, and mild exercise a person completes in a 7-day period. A weekly leisure-time activity score is calculated to categorize a patient’s activity level.^31^ The DASI is a validated 12-question survey designed to estimate a patient’s functional capacity.^32^ The Patient Activation Measure is a 13-item survey to measure a patient’s knowledge, skill and confidence in managing one’s own health and healthcare. Patients are categorized into 4 levels: Disengaged and overwhelmed, becoming aware but still struggling, taking action and gaining control, and maintaining behaviors and pushing further.^33^ DietID^™^ uses the patented Diet Quality Photo Navigation (DPQN^®^), which uses pattern recognition instead of dietary recall or food logs to provide a dietary assessment.^34^ Patients are presented composite images of established dietary patterns and are asked to select images most like their own, current food intake until a best fit is achieved. Outputs include the Healthy Eating Index (HEI-2020) and nutrient analysis. The ASA24 is a self-administered 24-hr recall dietary assessment developed by the National Cancer Institute.^35^

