#### Laboratory data

Laboratory results to measure safety will be conducted at baseline, 6 weeks in the study, and 12 weeks in the study. Laboratory values to be obtained include liver function tests (AST, ALT, ALP, Total bilirubin) and kidney function (creatinine, eGFR, BUN, cystatin C).

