### Creatine/whey protein and placebo supplementation

Creatinine/whey protein and non-sugar based placebo powder supplementation will be provided at a dosage of 5g creatine and 35g whey protein daily or one daily serving of placebo powder respectively given 30 minutes prior to exercise on exercise days and anytime on days without exercise.^36^ This dose was determined based on general doses of creatine and/or whey protein supplementation provided in other studies among athletes and older adults.^27, 37^ Kidney and liver function will be evaluated at baseline, 6 weeks, and 12 weeks. Participants who develop a ≥ 5 times increase from baseline or upper limit of normal of AST/ALT, ≥ 1.5 times increase of creatinine, or any grade 3–4 laboratory abnormality will be evaluated for dose reduction or discontinuation. If patients experience moderate gastrointestinal symptoms interfering with daily activities, persistent muscle cramps, or ≥ 5 pound weight gain over 1 week with concern for fluid retention, participants will initially undergo reduction of supplementation to half dose at week 1 week and re-escalation to full dose at week 2 if symptoms resolve. If symptoms persist at half dose, supplementation is discontinued and patients will continue STRIVE digital health programming.

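### The renal exclusion screens only for hemodialysis; a baseline eGFR limit would be a cheap safety improvement that uses tests already planned

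*Protocol article*

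**What the plan says.** Exclusion Criteria lists, with its reason, "2) hemodialysis due to concern for possible renal effects of creatine/whey protein supplementation". It is the only criterion in the list that names a kidney condition or treatment.

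Laboratory data states: "Laboratory results to measure safety will be conducted at baseline, 6 weeks in the study, and 12 weeks in the study". The panel includes "kidney function (creatinine, eGFR, BUN, cystatin C". The section on supplementation repeats the schedule: "Kidney and liver function will be evaluated at baseline, 6 weeks, and 12 weeks".

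On sequence, Assessments says "Baseline assessment will be completed prior to pre-enrollment into the ramp-up period", and Randomization says "Patients who meet eligibility criteria and complete the two-week ramp-up period will be randomized". The baseline assessment therefore comes before the two-week ramp-up, and allocation comes after it.

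The same supplementation section sets one active dose for everyone, 5 g creatine with 35 g whey protein daily. Its laboratory rule covers participants who develop a liver enzyme rise, or a rise of at least 1.5 "times increase of creatinine, or any grade 3–4 laboratory abnormality will be evaluated for dose reduction or discontinuation".

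**The concern.** The stated worry is that the product may affect the kidney. A patient with severe impairment short of hemodialysis still has kidney function to lose, so the worry applies to that patient at least as much as to one already on dialysis. As published, the rule admits the first and removes only the second.

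What is at stake is the safety of a small, identifiable group. Baseline tests that would identify these patients are already scheduled before randomisation, but nothing in the published criteria or dosing rules acts on them.

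**Working it through.** No figure in the plan depends on this criterion, so the check is mainly a reading of the rules side by side.

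**1. Does another entry rule cover severe kidney impairment without hemodialysis?**

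- Inclusion Criteria: age, cirrhosis, LFI, variceal screening, device access, availability and ramp-up engagement. There is no creatinine or eGFR limit.
- Exclusion (1): inability to take the product safely, but only because of milk protein allergy.
- Exclusions (3) and (4): device and language.
- Exclusion (5): supplemental oxygen, partly because the product may cause edema. The list does screen on product risk.
- Exclusion (6): conditions that make home exercise unsafe. None of the listed examples is renal.
- PAR-Q+: presented as an exercise screen.

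None of these covers it.

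**2. Does a starting-dose rule cover it?** No. The half-dose step in the supplementation section responds to symptoms or rapid weight gain on treatment. The laboratory rule responds to changes that develop on study.

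**3. Is the information available in time?** Yes. Study design and setting says "Patients are evaluated in-person at baseline prior to the ramp-up period, at 6 weeks after enrollment into STRIVE", and randomisation follows the ramp-up. If the baseline bloods are drawn with the rest of the baseline assessment, the results have at least two weeks to arrive before allocation. On the same assumption, the next scheduled kidney test comes at least 2 + 6 = 8 weeks after the baseline one, and six of those weeks are on product.

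**4. Can the on-study creatinine trigger stand in for an entry limit?** Assume that eGFR moves inversely with creatinine and that the trigger means 1.5 times baseline creatinine. Then

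eGFR at trigger = entry eGFR / 1.5.

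| Assumed entry eGFR (mL/min/1.73 m2) | eGFR when the trigger is met |
|---|---|
| 45 | 45 / 1.5 = 30 |
| 30 | 30 / 1.5 = 20 |
| 15 | 15 / 1.5 = 10 |

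If the wording instead means a rise of 150%, so that creatinine reaches 2.5 times baseline, the middle row becomes 30 / 2.5 = 12. A relative trigger allows the same proportional loss whatever the starting level. The entry values are assumed. The table shows how the trigger behaves; it does not show harm or how often the situation would arise. The grade 3–4 trigger may be met earlier, but the article does not name its grading scale, so this cannot be worked out.

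**5. Is the design calculation affected?** No. With a difference of 0.3, an SD of 0.75, two-sided alpha 0.05 (sidedness assumed) and 80% power, the normal approximation gives 99 per arm. The t-test solution is 99.08, hence 100 per arm and 200 in total, as the article states. The renal criterion does not enter this calculation.

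**The case against.** The strongest reply is that nothing here is inconsistent. Giving a reason for excluding one group does not oblige a trial to exclude everyone to whom the reason might apply. The oxygen criterion has the same form: it cites edema without removing every patient at risk of edema. That is right, and a reader who inferred that the article contradicts itself would be going too far.

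Second, the renal concern is managed by monitoring. Besides the week 6 and week 12 bloods and the two laboratory triggers, there are weekly coordinator check-ins for safety, weekly contact with a physician or exercise specialist, a weight-gain rule, and an independent board that reviews serious adverse events monthly and takes part in discontinuation decisions. It would be wrong to infer that such patients are unprotected. What remains is that every one of these acts after dosing has begun, and none adds a scheduled kidney test before week 6.

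Third, the article gives no evidence that this dose is unsafe in non-dialysis kidney impairment. That also stands: it speaks only of possible effects. Equally, the support it cites is not stated to cover these patients. The dose comes from studies in athletes and older adults, and the safety remark in the Discussion concerns older adults living in the community.

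Fourth, the full protocol is not shown and may contain a laboratory limit. This lowers confidence. It does not change what the published numbered criterion says when it is followed exactly.

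Finally, broad entry might be deliberate. The article states breadth for Child Pugh class, not for kidney function.

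**Conclusion.** The point holds as a worthwhile, inexpensive safety improvement, with medium confidence. As published, the renal exclusion removes only patients on hemodialysis, and the planned baseline kidney results decide neither entry nor starting dose. A patient with severe impairment not on hemodialysis can start the full daily dose, with the first scheduled kidney test on product at week 6.

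Its size cannot be given as a number of patients, because the article has no data on kidney function in the target population. A reader might infer that participants will be harmed, or that the trial's result is in doubt. The documents support neither: they contain no evidence of harm at this dose in such patients, and the primary estimate and the sample size do not depend on the criterion. The conclusion rests on the published criteria being the operative ones.

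**What to change.** Extend exclusion (2) to read: hemodialysis, or baseline eGFR (preferably cystatin C-based) below 30 mL/min/1.73 m2. The limit of 30 is an assumption, since the article gives none. The clinical team should confirm or replace it with a single figure before enrolment and write that figure into the criterion. Keep the creatinine and grade 3–4 triggers unchanged as the on-study safeguard.

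The change is one line of eligibility text. It needs no new test or visit, because the panel is already planned at baseline and the ramp-up leaves time for the result. If the result is read before the ramp-up, ineligible patients are also spared that effort. The downside is a somewhat narrower population at a single center that already screens on LFI, PAR-Q+ and 80% ramp-up engagement. The loss of eligible patients cannot be estimated from the article. The target of 200 randomised does not change, though reaching it may take more screening.

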### Randomization

Patients who meet eligibility criteria and complete the two-week ramp-up period will be randomized using a 1:1 allocation ratio to placebo vs creatine/whey protein supplementation and permuted blocks of sizes of lengths 2 and 4 by the statistician. Randomization will be stratified by Child Pugh score (A, B, C) and gender (women, men). Six randomization lists will be generated by the study biostatistician using R “randotools” package for each combination of stratification factors: A/female, B/female, C/female, A/male, B/male, C/male. The randomization list will be used to assign eligible and consented participants to one of the two trial arms of the study to the pharmacy. Patients will receive a blinded box of creatine/whey protein vs placebo in single daily sachets with instructions on use.

